## Abstract

**Background:**

Mild cognitive impairment and mild dementia progressively compromise the ability of people to live independently and can have a negative impact on their quality of life. Within the current European Active and Assisted Living programme (AAL), project TV-AssistDem has been developed to deliver a TV-based platform service to support patients with mild cognitive impairment or mild dementia and provide relief to their caregivers. The application is intended to be used daily at home, mainly by the participants themselves, with the help of their informal caregivers. The aim of this study is to evaluate the effectiveness of TV-AssistDem to improve quality of life in people with mild cognitive impairment or mild dementia.

**Methods:**

This is a 12-month European multicentre randomized controlled trial which will be performed in two countries: Spain and Romania. Two hundred and forty older adults will be recruited using identical inclusion/exclusion criteria. The primary outcome will be the change from baseline of TV-AssistDem on patient quality of life at 12 months. The secondary outcomes will be the changes from baseline of: 1) informal caregiver quality of life, 2) informal caregiver burden, 3) patient treatment adherence, 4) patient treatment compliance, 5) patient functional status, and 6) healthcare cost-effectiveness at 12 months. Patients in the intervention group will have access to an interactive platform which offers remote assistive services through a device connected to the television. The core services of the platform are: 1) Calendar and reminders, 2) Health monitoring and data transmission to a health server and 3) Videoconference; service-oriented applications are: 4) Cognitive stimulation; 5) Reminiscences; and 6) Patient and caregiver healthcare education. The analysis will be made following an intention-to-treat procedure. Linear and Generalized Mixed Model analysis will be performed.

**Discussion:**

We hypothesize that the regular use of TV-AssistDem will result in an improvement in patient quality of life. The uniqueness of this home TV-based intervention lies on its widespread accessibility and its integrative approach to quality of life in people with mild cognitive impairment or mild dementia and their informal caregivers. However, several anticipated challenges will need to be faced: poor engagement and connectivity problems.

**Trial registration:**

ClinicalTrials.gov Identifier NCT03653234, Date of registration: 31 August 2018.

## Background

Population ageing within Europe has major social and economic consequences. The burden of non-communicable disease and disability increases with age, exerting pressures on health services and support systems for older people. One of the most devastating conditions that predominantly affects older people is dementia [1]. Dementia is an umbrella term describing a set of symptoms that occur when various diseases or conditions affect the brain, being the most common cause of dementia, Alzheimer’s disease. The symptoms that comprise dementia can vary greatly, with people often experiencing memory loss but also problems in communication and attention, anxiety and depression [2]. Mild cognitive impairment represents an intermediate state between normal cognitive changes when aging and the earliest clinical manifestations of dementia. It is a syndrome where decline in cognition in a person is greater than the level expected for his/her age and education level, but which does not interfere notably with activities of daily life. The distinction between dementia and mild cognitive impairment can be quite subtle [3]. Treatment options currently remain centered on symptomatic treatment. The main drugs prescribed for people with mild to moderate dementia are cholinesterase inhibitors. Anti-dementia drugs have not yet met the scientific community’s expectations.

There are currently about 10.5 million people in Europe with dementia, costing around 275 billion euros annually. Given that this number is expected to rise to 13.4 million by 2030, the challenge of dementia is likely to remain formidable [4]. Healthcare policies are therefore focused on extending the ability of older people to continue to live independently. This entails maintaining the quality of life (QoL) of people with mild cognitive impairment or mild dementia (PMCI/MD), as well as, working to reduce the costs of their care.

Living with dementia in the early stages can be burdensome for both those affected as well as their caregivers [5, 6]. Caring for PMCI/MD can compromise the informal caregiver’s own well-being and health due to a feeling of being overloaded in the caregiving role [7]. The well-being of the informal caregivers themselves and providing them with support is therefore essential [8].

The importance of including QoL as an outcome measure in dementia trials has been identified by the World Federation of Biological Psychiatry’s Old Age Taskforce [9]. QoL is multifactorial; consequently, in addition to “an individual’s perception of their position in life in the context of the culture and value system in which they live and in relation to their goals, expectations and standards and concerns.” [10], it also includes physical and mental health, social relations and participation in activities. Therefore, it cannot be determined solely by changes in cognition or other symptoms.

Systematic reviews focused on the effectiveness of interventions in QoL of PMCI/MD conclude that while pharmacological interventions seek changes in symptoms as a main outcome and have not been found to improve QoL, non-pharmacological interventions aimed at PMCI/MD living in their home and their caregivers have proven QoL improvement [9].

Information and Communications Technology (ICTs) studies focus on the use of assistive technologies to improve QoL in elderly people in general [11]. These technologies are computers, sensors, telemedicine, mobile applications of medication management, etc. The age-related digital divide and cognitive, sensorial and psychomotor impairment determine the use of certain ICTs in older people, such as tablets (e.g. losing the tablet or not being able to visually see the tablet’s screen). Television sets however, are standard devices with an extensive home penetration, being TV-based interventions more suitable for this population.

Three ICTs studies were identified which show QoL improvement in PMCI/MD and their caregivers. A recent clinical review on digital technologies used to monitor cognition, identified a range of digital systems, such as smartphones, smartwatches and smart homes, to assess and assist elderly demented, prodromal and preclinical populations. It highlights the need for additional research that validates the efficacy, utility and cost-effectiveness of these systems in patient populations [12]. However, there are few large evidence based studies on the effectiveness of these techs to improve QoL in PMCI/MD. These studies have small sample sizes, do not include QoL as a main outcome measure, or do not include valid QoL scales. Therefore, randomized controlled clinical trials with large samples are needed.

Since QoL also includes physical and mental health, follow-up of agreed recommendations from a health care provider in terms of medication and Activities of Daily Living (ADLs) will be crucial [13]. Patient adherence to prescribed medication is probably the most important therapeutic factor and a determinant of medication effectiveness and safety [14, 15]. Scientific literature reveals poor cognitive function as a risk factor of medication non-adherence [16]. Often, a patient’s ability to manage his or her medication is decisive regarding whether a patient has mild cognitive impairment or dementia, which is why assessing medication adherence is crucial [16].

Group Structured Cognitive Stimulation Therapy (CST) is recommended by the NICE-SCIE Guideline on Supporting people with Dementia and their caregivers [17]. Home-based CST is an opportunity for people with health/mobility problems or who dislike group therapy and increases accessibility for local areas which do not offer group therapy [18].

There has been a raise in the development of ICTs to improve or to enhance different domains to keep the independence or to support PMCI/MD like: reminders, cognitive training, geolocation devices, but all of them have focused in monitoring cognition with limited data on patient QoL.

The aim of this study is to deliver a TV-based platform service which will improve quality of life of people with mild cognitive impairment or mild dementia. Additionally, this technological solution seeks to improve caregiver quality of life and reduce caregiver burden, increase patient treatment adherence and compliance, reduce patient functional decline, and lower healthcare costs.

## Methods

### Aims

We refer to our TV-based Assistive Integrated Service intervention as TV-AssistDem. The main objective of this project is:
To evaluate the effectiveness of TV-AssistDem on quality of life among people with mild cognitive impairment or mild dementia after 12 months follow-up in comparison to controls. We hypothesize that the use of TV-AssistDem over 12 months can result in an improvement in quality of life when compared to a matched control group of patients not using TV-AssistDem.

The secondary objectives of this project are:
To evaluate the impact of TV-AssistDem on caregiver quality of life after 12 months of follow-up. We hypothesize that quality of life will be significantly improved in caregivers after the intervention when compared to matched controls over 12 months.To evaluate the impact of TV-AssistDem on caregiver burden after 12 months of follow-up. We hypothesize that burden will be significantly reduced in caregivers after the intervention when compared to matched controls over 12 months.To evaluate the impact of TV-AssistDem on patient treatment adherence after 12 months of follow-up. We hypothesize that treatment adherence will be significantly increased in patients in the intervention group when compared to matched controls over 12 months.To evaluate the impact of TV-AssistDem on patient treatment compliance after 12 months of follow-up. We hypothesize that treatment compliance will be significantly increased in patients in the intervention group when compared to matched controls over 12 months.To evaluate the impact of TV-AssistDem on functional status after 12 months of follow-up. We hypothesize that functional decline will be significantly reduced in patients in the intervention group when compared to matched controls over 12 months.To test the economic and financial impacts of using the TV-AssistDem after 12 months of follow-up. We hypothesize that after accounting for the estimated per patient costs of our intervention, patients in the intervention group will have significantly lower healthcare costs after 12 months follow-up when compared to matched controls over 12 months.

### Study design

This study is a multicentre randomised controlled trial and will be performed in two European countries: Spain and Romania. The participant centres are: the Spanish Health Research Institute of Malaga (IBIMA) and the Romanian NGO Home Care Association (Îngrijiri La Domiciliu).

### Setting

Patients will be identified from people with self-perceived cognitive impairment or caregiver’s perception of cognitive impairment that has been present for more than 6 months and who meet all the study eligibility criteria. The patients can be under primary care services, as well as, secondary care services, such as those who are being followed up in memory clinics, outpatient clinics, day hospitals or other components of specialist mental health, geriatric medicine and neurology services. The clinicians involved in identifying the patients will be physicians (primary care, psychiatry, neurology, and geriatrics), neuropsychologists and dementia and mental health nurses.

The identification process by the clinician will consist of screening, using information gathered from medical notes, clinical records and/or clinical consultations, for initial eligibility based on inclusion criteria. Patients will receive a brief explanation by their clinician. A member of the research team will contact the patient to see if they are willing to participate in the study, and if so, an appointment at their referral centre will be scheduled. Their primary caregiver must attend this visit.

At this first visit, the researcher will determine the patient’s eligibility and will explain the study in detail and answer any questions the patient or caregiver may have. After doing so, the patient’s ability to consent will be assessed following the Assessment of capacity to consent which includes the 5 fundamental principles of the Mental Capacity Act. In case of cognitive impairment or dementia, patients will be asked five questions regarding the information received as part of the decision-making process. Proxy consent of a legal representative or the caregiver will be required when the patient is not found capable. Both the patient and caregiver will give consent regarding their participation in the study. Once given consent, the patient will be randomized into the intervention or control group. Follow-up will begin after the randomization and will be determined by the group allocation. Within one to two weeks after being included in the study, patients allocated in the intervention group will be scheduled a visit for TV-AssistDem installation and training.

Patients will be assessed for 12 months. After the baseline visit in which all the variables of the study will be collected, follow-up visits will be carried out every 6 months in both the control group and the intervention group. In these follow-up visits, researchers will assess the QoL of the PMCI/MD, adherence and compliance to prescribed medication, functional status, and service utilization. Researchers will also evaluate the QoL of caregivers and their burden. In addition, in the intervention group, TV-AssistDem user-behaviour data will be collected and usability will be evaluated.

Recruitment is scheduled to start in March 2019 and end in May 2019. Follow-up assessments will be ongoing and will be completed mid-2020.

### Participants

Two hundred forty participant dyads in two European countries (Spain and Romania). The participant dyads will comprise the PMCI/MD and their informal caregivers, defined as the person who is unwaged for this role and who spends the most time with the patient and whom the patient declares that he/she is his/her informal caregiver, for care or support of care, and who does not take part in a formal network of organized care.

A patient will be eligible for inclusion in this trial only if all following criteria apply:
Patients are over sixty years of age.Self-perceived cognitive impairment or caregiver’s perception of cognitive impairment that has been present for more than 6 months.Patients score 23–27 points on Mini-Mental State Examination (MMSE).Patients live independently.Patients have an informal caregiver.Patients who take pharmacological treatment for chronic conditions during study period and are in charge of their own medication.The place where patients live has enough wireless or phone network connectivity to enable them to use TV-AssistDem platform on a daily basis.Patients agree to be part of the study by giving signed written consent.

A patient will not be eligible for inclusion in this trial if any of the following criteria apply:
Patients score above 11 on the Geriatric Depression Scale (GDS-15).Patients have a terminal illness with less than 3 years expected survival.Patients have specific conditions reducing their physical ability to use the application to a point that makes their participation in the project impossible (the nature of the conditions will be recorded in such cases).

### Outcome measures

The primary outcome measure is the change in patient quality of life measured with the Quality of Life-Alzheimer’s Disease Scale (QoL-AD) [19–22]. Additional assessments will be used for secondary outcomes: caregiver quality of life and burden, patient treatment adherence and compliance, patient functional status and service utilization. TV-Assist Dem usability and other covariables will also be collected.

Patients will be assessed at baseline and at 6 months and 12 months after the beginning of the intervention. The assessments will be conducted under standardized conditions at the study centres.

#### Primary outcome

##### Patient quality of life

QoL-AD is an instrument specifically designed to measure QoL in PMCI/MD from the perspective of both the patient and the informal caregiver. It is a 13-item measure, which includes assessments of the person’s relationships with friends and family, financial situation, physical condition, mood, memory, and an overall assessment of life quality. Response are 4-point multiple choice options (1 = poor, 2 = fair, 3 = good, 4 = excellent). Scale scores range from 13 to 52, with higher scores indicating greater quality of life. PMCI/MD may lose cognitive function during the study to the extent that they are unable to complete the assessments themselves. For this reason, informal caregivers will also complete the QoL-AD, in parallel and on behalf of the PMCI/MD, from the start of the study. QoL-AD will be assessed via interview with the patient and via self-completion with caregivers at baseline and then at 6 and 12 months.

#### Secondary outcomes

##### Caregiver quality of life

EuroQoL-5D-5 L [23, 24] is a standardized generic instrument consisting of a descriptive system and a visual analogue scale (VAS).

The descriptive system comprises 5 dimensions covering mobility, self-care, usual activities, pain/discomfort and anxiety/depression. Each dimension has 5 levels: no problems, slight problems, moderate problems, severe problems and extreme problems. A 1-digit number expresses the level selected for that dimension. The digits can be combined into a 5-digit number that describes the patient’s health state.

The VAS records the patient’s self-rated health on a vertical scale, where the endpoints are ‘The best health you can imagine’ and ‘The worst health you can imagine’.

EuroQoL-5D-5 L has been shown to correlate well with QoL-AD, indicating that using both measures side-by-side is compatible [19]. Both will be completed by the patient and caregiver at baseline and then at 6 and 12 months.

##### Caregiver burden

The Zarit Burden Interview (ZBI-12) [25, 26] will be used to evaluate the informal caregivers’ burden. The ZBI-12 is a 12-item scale with each answer chosen from a 5-point Likert scale (Nearly always = 4, Quite frequently = 3, Sometimes = 2, Rarely = 1, Never = 0). It is a shortened version of the original scale, was developed specifically for informal caregivers of PMCI/MD and covers issues such as caregiver stress and the degree to which caring is affecting their health and social life. Total score ranges 0 to 48 (0–10 = no to mild burden, 10–20 = mild to moderate burden > 20 = high burden). It will be administered via interview with the informal caregiver at baseline and then at 6 and 12 months.

##### Treatment adherence

The dose/pill count is the number of pills or doses taken divided by the prescribed ones, multiplied by 100 (expressed as a percentage) [27, 28]. According to Haynes et al. recommendations [32], a good adherence is considered when the result of counting is between 80% (a 20 % of doses/pills missed) and 110% (the patient takes 10 % more doses/pills) of dose/pill prescribed [29].

The documented prescription for medications will be compared with the number of pills taken (or pill equivalents) 30 days before assessment day. Dyads will be asked to bring to the visit any documentation related with their prescription history, all the pills and empty medication packaging from the previous 30 days, so that the researcher can undertake the medication count. Drugs considered to evaluate adherence will be anti-dementia drugs and other chronic diseases treatment that influence the evolution of dementia (e.g. drugs for cardiovascular diseases, antidiabetics, anticoagulants, antihypertensive and antidepressants). This assessment will be undertaken at baseline and then at 6 and 12 months.

##### Treatment compliance

The Medication Assessment Questionnaire test was originally developed to assess medication compliance in patients with hypertension [30]. Since the test was introduced it has been used in the assessment of therapeutic compliance in different diseases and has been validated for Spanish population [31]. It consists of 4 contrast questions with dichotomous yes/no responses, reflecting the patient’s behaviour regarding compliance. They are intended to assess whether the patient adopts correct attitudes regarding treatment for their disease; it is assumed that if the attitudes are incorrect the patient is non-compliant. It will be administered at baseline and then at 6 and 12 months.

##### Functional status

Lawton Instrumental Activities of Daily Living Scale (IADL) [32] scale will be used to evaluate functional status in the PMCI/MD. The IADL is an interview format scale of 8-items covering instrumental activities, which are required for independent living: ability to use telephone, shopping, food preparation, housekeeping, laundry, mode of transportation, responsibility for own medications and ability to handle finances. Because these instrumental functions are usually lost before more basic ADLs functions (such as bathing, eating, and using the toilet), assessment of IADL may identify incipient decline in older people who might otherwise appear capable and healthy. The score ranges from 0 (low function, dependent) to 8 (high function, independent) for women and 0 through 5 for men to avoid potential gender bias. IADL will be administered via interview to the PMCI/MD and their caregiver at baseline, and then at 6 and 12 months.

##### Service utilization

The Client Service Receipt Inventory (CSRI) [33, 34] scale will be used to evaluate the service utilization. This scale is an internationally used method for gathering data on service utilization and other domains relevant for economic analysis of mental health care. It has five sections: background client information, accommodation and living situation, employment history, earnings and benefits, a record of services usually used and information about informal caregiver support. The sections assessed will be consultations, admissions and visits in the last year, grouped into subsections according to hospital, specialist, primary or home care. Treatment related to hospital admissions or illness exacerbation will also be assessed. It’s adaptability ensures it is compatible with the research aims, context, participants’ likely circumstances, and the quantity and precision of information required. The CSRI will be administered via interview with PMCI/MD at baseline and at 12 months.

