##### Usability evaluation

The System Usability Scale (SUS) [37, 38] will be used to address how well patients learn and use TV-AssistDem. It is a simple, 10-item scale giving a global view of subjective usability. The respondent indicates the degree of agreement or disagreement with each statement on a 5-point Likert scale with a score range of 0 to 100. The SUS scale will be used after the patients have had an opportunity to use TV-AssistDem before any debriefing or discussion takes place at 6 and 12 months.

The collected variables and data collection time are presented in Tables 1 and 2.

**Table 1 Tab1:** Patient’s data collection table

Assessment	Outcome variable	Screening	Baseline	6 months	12 months
Informed Consent	NA	X			
Capacity to Consent	NA	X			
Mini-Mental State Examination	NA	X		X	X
Geriatric Depression Scale	NA	X		X	X
Sociodemographic data	NA		X	X	X
Medical history	NA		X	X	X
Quality of Life-Alzheimer’s Disease Scale	Primary		X	X	X
EuroQoL-5D-5 L	Secondary		X	X	X
Medication Assessment Questionnaire	Secondary		X	X	X
Lawton Instrumental Activities of Daily Living Scale	Secondary		X	X	X
Client Service Receipt Inventory	Secondary		X		X
System Usability Scale	NA			X	X

*NA* = non-applicable

**Table 2 Tab2:** Caregiver’s data collection table

Assessment	Outcome variable	Screening	Baseline	6 months	12 months
Informed Consent	NA	X			
Caregivers data	NA	X			
Quality of Life-Alzheimer’s Disease Scale	Primary		X	X	X
EuroQoL-5D-5 L	Secondary		X	X	X
Zarit Burden Interview	Secondary		X	X	X
Lawton Instrumental Activities of Daily Living Scale	Secondary		X	X	X

*NA* = non-applicable

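### Service use, a main input to the cost outcome, is collected by one-year recall from the cognitively impaired patient with no caregiver as second informant, and its timing is stated in two ways

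*Protocol article*

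**What the plan says.** The Service utilization section names one respondent and two time points: "The CSRI will be administered via interview with PMCI/MD at baseline and at 12 months". It also fixes the content and recall window: "The sections assessed will be consultations, admissions and visits in the last year". The data collection tables agree. Table 1 (patients) lists the "Client Service Receipt Inventory" at baseline and 12 months, and Table 2 (caregivers) does not list it.

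The caregiver is nevertheless part of the trial: "The participant dyads will comprise the PMCI/MD and their informal caregivers". For the primary outcome the protocol foresees a reporting problem: "PMCI/MD may lose cognitive function during the study to the extent that they are unable to complete the assessments themselves". It responds by adding a proxy: "informal caregivers will also complete the QoL-AD, in parallel and on behalf of the PMCI/MD, from the start of the study". The Functional status section has both patient and caregiver interviewed for the IADL.

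On timing, the Setting section includes service utilization among the assessments at the follow-up visits held every 6 months. That does not match the Service utilization section or Table 1.

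**The concern.** The CSRI places a heavy demand on memory: a full year of contacts across hospital, specialist, primary and home care. The respondents have MMSE scores of 23–27 and cognitive impairment noticed by themselves or their caregiver for more than six months. The protocol brings in the caregiver for two other instruments but gives this one no second informant.

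Two things can follow. Contacts may be left out by patients who can still be interviewed. Patients who can no longer be interviewed have a caregiver QoL-AD to fall back on but no CSRI, so cost data may be lost in those who decline most.

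These data feed the secondary hypothesis in Aims that costs will be lower in the intervention group. They also feed the Economic analysis, whose cost items include outpatient and emergency visits and hospital admissions.

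**Working it through.** **1. Is there a figure to reproduce?** No. The document gives no recall accuracy, no expected cost and no sample size for the cost outcome. The sample size rests on the QoL-AD and is not affected.

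**2. Safeguards, instrument by instrument**

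| Instrument | Recall window | Second informant or documents |
|---|---|---|
| QoL-AD | not stated | caregiver completes it in parallel |
| IADL | not stated | patient and caregiver interviewed |
| Pill count | 30 days | prescriptions and packaging brought by the dyad |
| CSRI | one year | none stated |

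The CSRI has the longer of the two stated windows and the least support.

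**3. Would a stated check catch omissions?** The section on validity and quality of data compares 5% of case report form data with the researcher's own records. That tests transcription. A visit that the patient did not mention would be absent from both sources.

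**4. Equal under-reporting (illustration).** Let *C* be the true control service cost, *d* the true relative difference, and *r* the share of use reported in both arms.

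- Observed ratio = *r* × *C*(1 + *d*) / (*r* × *C*) = 1 + *d*, so it is unchanged.
- Observed absolute difference = *r* × *C* × *d*, so it shrinks by 1 − *r*.

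With *C* = 1000 and *d* = −10% (both assumed), the true saving is 100:

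- *r* = 0.90: 90 (10% lost)
- *r* = 0.80: 80 (20% lost)
- *r* = 0.70: 70 (30% lost)

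The cost hypothesis allows for the per-patient cost of the intervention, which does not depend on patient recall. That cost is deducted in full from a saving that has been scaled down.

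**5. Unequal under-reporting (illustration, both directions).** Observed ratio = (1 + *d*) × *r*_I / *r*_C, where *r*_I and *r*_C are the shares reported in the intervention and control arms.

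| Control / intervention share reported | No true difference | True 10% saving |
|---|---|---|
| 0.80 / 0.90 | 0.90/0.80 = 1.125, +12.5% | 0.90 × 0.90/0.80 = 1.0125, about +1% |
| 0.90 / 0.80 | 0.80/0.90 = 0.889, −11.1% | 0.90 × 0.80/0.90 = 0.80, −20.0% |

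A 10-point gap could hide or create a difference of about 10%. This shows sensitivity only. Nothing in the document gives the size or direction of any gap.

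**6. Timing.** Setting implies collection at 6 and 12 months, whereas the Service utilization section and Table 1 give baseline and 12 months. If a 6-month collection kept a one-year window, it would reach back 6 months before baseline and overlap with the 12-month interview (12 + 12 − 18 = 6 months counted twice). The schedule and the window have to be settled together.

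**The case against.** **Mild impairment.** Participants live independently and manage their own medication, and no recall accuracy is given. A reader might infer that costs will certainly be under-reported. The document does not support that; incomplete reporting is likely, not certain.

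**Bias between arms.** A reader might also infer that the platform's calendar, reminders and health monitoring improve recall in one arm and so bias the comparison. That is conjecture. The monitoring function records vital signs such as blood pressure and weight, not service contacts, and nothing says that the calendar keeps a history of consultations or admissions. The calendar also serves the dyad, so a joint interview would not remove such an asymmetry if it existed.

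**Other cost items.** Medication is also costed and need not rest on CSRI recall. This stands: the point concerns consultations, visits and admissions.

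**Purpose of the proxy QoL-AD.** It was added because patients may become unable to respond, not to improve recall. This is true, but inability to respond affects the CSRI as well.

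**Condensed article.** Limitations mentions a researchers' manual with details for each variable, and the article does not say that the patient is interviewed alone. Practical support could be described there. But the article does name the CSRI respondent, both tables agree, and the IADL text names the caregiver where the caregiver is meant. This is a stated choice rather than an omitted detail.

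**Clinical records.** It is tempting to ask for a check against records, since patients are screened "using information gathered from medical notes, clinical records and/or clinical consultations". That describes identification by the clinician. Access for outcome collection is not documented, and one centre is a home care association.

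**Conclusion.** The point holds as a design weakness in one secondary outcome. The only named informant for a year of service use is a patient with perceived cognitive impairment, although the caregiver is enrolled, is assessed at the same visits, and is used for the QoL-AD and IADL. Reporting is likely to be incomplete, and there is no fallback for patients who become unable to respond.

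If 70–90% of use is reported equally in both arms (an assumption), the absolute saving in service cost is understated by 10–30%, while the relative difference is unchanged. Bias between arms is possible in either direction, but the document does not establish it and the conclusion does not depend on it. The primary outcome and sample size are untouched.

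Separately, the document contradicts itself on whether service use is collected at 6 months. The change should be made, but the trial's main conclusion does not hang on it.

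**What to change.** 1. In Service utilization, state that the CSRI is administered to patient and caregiver jointly, in both arms, at the same visits, and that the caregiver answers where the patient cannot.
2. Add the CSRI row to Table 2.
3. Reconcile Setting (service utilization at the six-monthly visits) with Service utilization and Table 1 (baseline and 12 months only). If a 6-month collection is intended, state a recall window that matches the interval since the previous interview.

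The cost is a few lines of text and a few extra minutes per visit. The caregiver is already interviewed at baseline and 12 months for the burden scale and the IADL, so no extra visit is needed. Caregiver recall is also imperfect, so a joint interview reduces the error without removing it, and it would not correct a difference in recall between arms if one existed.
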